## Abstract

**Introduction:**

Only 30%-40% of patients with first-episode depression recover after taking antidepressants. Acupuncture is a clinically recognized treatment for depression, but its effect on first-episode depression remains unknown. This randomized controlled trial is designed to investigate the efficacy and safety of electroacupuncture (EA) compared with escitalopram (ESC) in treating patients with mild to moderate first-episode depression.

**Methods and analysis:**

This is a multi-site, single-blind, randomized controlled trial with two parallel arms. A total of 204 eligible patients will be randomly allocated to two groups: the EA group (receiving EA treatment with placebo drugs) and the ESC group (receiving escitalopram and sham acupuncture treatment). Treatment will last 12 weeks, with 3 sessions per week for the first 8 weeks, decreasing to 2 per week for the remaining 4 weeks. The primary outcome will be the score of the 17-item Hamilton Depression Rating Scale (HAMD-17), and the secondary outcomes will include depression recovery rate, depression remission rate, Patient Health Questionnaire-9 (PHQ-9), 36-Item Short Form Survey Instrument (SF-36), and the dose and frequency of ESC. The Treatment Emergent Symptom Scale (TESS) will be used to assess all adverse effects. Full details of the statistical analysis plan for the primary and secondary outcomes will be described in this article.

## Introduction

Depression is an emotional disorder that endangers human physical and mental health and is characterized by persistent sadness and/or loss of pleasure in previously enjoyable activities. Approximately 300 million people worldwide suffer from depression, which has become a major cause of disability and significantly contributes to the global disease burden (1, 2). Depression is the most common mood disorder in China, with a lifetime prevalence of 3.4% and a prevalence of 2.1% at twelve months (3).Selective serotonin reuptake inhibitors (SSRIs) are currently the first-line agents for treating depression. However, due to the complex etiology, only 30%-40% of patients with first-episode depression achieve clinical recovery after treatment with antidepressants alone (4, 5). While SSRIs can enhance the effectiveness in treating depression, it is important not to disregard their known adverse effects, including nausea, vomiting, tolerance, addiction, excessive sedation, and neurological damage (6, 7). Thus, it is urgent to develop an effective and safe treatment for patients with mild to moderate first-episode depression, especially for those potential non-responders.

In contrast to therapy with SSRIs alone, manual acupuncture (MA) as an add-on therapy for SSRIs can effectively improve the Hamilton Depression Scale (HAMD-17) scores and depression self-rating scale (SDS) scores to a greater extent (8). A randomized controlled trial has also shown that the efficacy of electroacupuncture (EA), a combination of acupuncture and low-pulse electrical stimulation, is not less than that of antidepressants (8, 9). However, evidence remains insufficient in relation to the comparison between the efficacy of EA and SSRIs, and thus the question of whether EA is not inferior to SSRIs in treating first-episode depression remains inconclusive.

We therefore designed this patient-blinded, randomized, and placebo-controlled trial with a sufficient observation period in Shanghai, China. The main objective of this trial is to explore whether EA is a viable alternative to SSRIs for patients diagnosed with mild to moderate first-episode depression.

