### Design

This is a multi-center, patient-assessor-blinded, randomized, and controlled trial designed to evaluate the efficacy and safety of EA treatment in patients with mild to moderate first-episode depression and to compare the therapeutic effect between EA and ESC.

We will conduct this study at 4 centers, including Shanghai Municipal Hospital of Traditional Chinese Medicine, Shanghai Mental Health Center, Shanghai Pudong New District Nanhui Mental Health Center, and Shanghai Xuhui District Central Hospital. A total of 204 patients who meet the inclusion criteria will be recruited and randomly assigned into either group, receiving EA treatment with placebo drugs or ESC with sham acupuncture (SA) treatment. After a one-week baseline evaluation, participants will enter a nine-month observation period in this trial. Participants will receive the EA or SA treatment three times a week (every other day) for the first 8 weeks and twice a week (every two days) for the final 4 weeks. Participants will be assessed at the following time points: baseline (1 week before treatment), the 1st month of treatment (4 weeks after treatment starts), the 2nd month of treatment (8 weeks after treatment starts), the end of treatment (12 weeks after treatment starts), and follow-up (1 month, 3 months, and 6 months after treatment ends). All participants will complete the self-rated scales to assess their mental state and quality of life (see the detailed trial process in **Figures 1**, **2**). Throughout the trial, we will adhere to the Standards for Reporting Interventions in Clinical Trials of Acupuncture (STRICTA).

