### Sample size calculation

The non-inferiority hypothesis is based on the results of a previous study (11). HAMD-17, as the primary outcome, decreased by 11.3 points in the premedication group and by 10.2 points in the EA group, with an equal standard deviation of 11.5 points. Following these parameters, the proposed non-inferiority boundary is set at -4 points, with a level one type I statistical error equivalent to 0.025 and a desired statistical power standing at 80%. These calculations are supported by the analytical tools implemented in PASS 15.0. The results were obtained for a required sample size of 81 cases per group, and considering a 20% drop rate, 102 cases need to be included in each group, totaling 204 cases. The formula employed to determine the sample size in this trial was listed as:

$${\text{n}}_{\text{A}}={\text{k}}_{{\text{n}}_{\text{B}}}\;\text{and}\;{\text{n}}_{\text{B}}=\left(1+\frac{1}{\text{k}}\right){\left(\sigma \frac{Z_{1-\alpha }+Z_{1-\beta }}{\mu_{A}-\mu_{B}-\delta }\right)}^{2}$$

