### Statistical analysis

Analyses will be conducted on the intention-to-treat (ITT) population, which comprises all qualified participants who meet the inclusion criteria, have received the intervention at least once, and have provided at least one outcome assessment. In statistical analysis, any missing primary outcome data will be replaced by the last observed data point, in accordance with the ITT principle. Additionally, a Per-Protocol Set (PPS) analysis will be employed to assess those participants who completed the trial without significant protocol violations. Data analysis for this study will be performed using the statistical software SPSS V.24.0. Descriptive statistical analysis will be used for all demographic and clinical characteristics of subjects, such as sex, age, and weight. We will validate the homogeneity of demographic characteristics and examine the variables between the two groups. The number of patients who change their medication dosage will also be counted, and the variations between the two groups and within each group will be analyzed. If measurement data follows a normal distribution and has homogeneity of variance, the data values will be reported as mean ± standard deviation (MD ± SD). Covariance analysis will be used to compare the data across different groups. If the data does not adhere to the assumed normal distribution, the median values (P25, P75) will be used to characterize it. The Mann-Whitney U nonparametric test will be used to compare between groups. The mean ± standard deviation will be used for the description of the continuous variables. Qualitative data will be expressed in terms of frequency and percentage. The student’s t-test will be utilized for comparing measurement data between two groups from baseline to the 6-month follow-up, while the rank sum test will be used for ranked data, and the χ2 test will be used for analyzing categorical data. A paired t-test was used for comparisons before and after treatment within a group, and an analysis of variance was used for comparisons among different groups. Repeated-measurement analysis of variance was used to compare groups at multiple observation points. A significance level of 2.5% will be used for all statistical analyses, using two-tailed testing. Subgroup analysis will be conducted to examine differences between different genders and across various age brackets.

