
## Conclusion

In summary, we will strictly adhere to the CONSORT statement and STRICTA recommendations to ensure standardized acupoint selection, manipulation, evaluation, and therapist clinical experience. As a multi-center RCT in a first-line city, we expect that this trial will validate the effectiveness and safety of EA as a clinical intervention for mild to moderate first-episode depression, which will address the gap left by SSRIs and provide a low-risk, beneficial non-drug therapy for patients with depression.

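### The trial is active-controlled and double-dummy, not placebo-controlled, and its EA-versus-ESC contrast alone cannot support the separate claims that EA is efficacious or effective

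*Protocol article*

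**What the plan says.** **Label.** The Introduction says: "We therefore designed this patient-blinded, randomized, and placebo-controlled trial with a sufficient observation period in Shanghai, China".

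**Arms.** The Abstract describes a "single-blind, randomized controlled trial with two parallel arms". The Design section gives the arms as "receiving EA treatment with placebo drugs or ESC with sham acupuncture (SA) treatment". The EA group and ESC group sections confirm this: starch tablets accompany real EA, and non-penetrating needles with the stimulator set to zero accompany escitalopram. The Discussion itself describes the SSRI as a positive control.

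**Aims and claims.** The Hypothesis section is confined to non-inferiority of EA to ESC. The Design section goes further and says the trial is "designed to evaluate the efficacy and safety of EA treatment in patients with mild to moderate first-episode depression and to compare the therapeutic effect", which makes efficacy an aim alongside the comparison. The Conclusion says "we expect that this trial will validate the effectiveness and safety of EA as a clinical intervention for mild to moderate first-episode depression".

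**Analysis.** Besides the between-group methods, the Statistical analysis section includes: "A paired t-test was used for comparisons before and after treatment within a group".

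**Margin.** The Sample size calculation relies on an earlier study in which "HAMD-17, as the primary outcome, decreased by 11.3 points in the premedication group and by 10.2 points in the EA group", with an SD of 11.5 in both groups. On those parameters it sets the boundary at -4 points. It cites no effect of ESC over placebo. The limitations in the Discussion do not mention the lack of a placebo reference.

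**The concern.** A placebo-controlled trial lets the reader attribute a difference from control to the treatment. This trial has no such control. Its two arms yield one randomised comparison, which answers whether EA is worse than ESC by more than the margin. Whether EA works at all is a different question, and only two routes to it remain in the document.

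The first is the before-after change within the EA arm. Patients enter on a HAMD-17 score of 17 to 24 and attend 32 sessions. Natural course, regression to the mean and attention can all lower the score whatever EA does.

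The second is indirect: if ESC is known to beat placebo by more than the margin, an EA that is non-inferior to ESC must itself have some effect. That argument needs a stated ESC-over-placebo effect, and the document gives none.

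At stake is the published conclusion. A non-inferiority result with a strongly significant fall in the EA arm could be reported as showing that EA is effective, when the data cannot show that.

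**Working it through.** **1. Arms against label.**

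| | Active tablet | Placebo tablet |
|---|---|---|
| Real EA | none | EA group |
| Sham needle | ESC group | none |

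The placebo-tablet-with-sham-needle cell is empty, so the design is active-controlled and double-dummy.

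**2. The plan's own sample size.** With the formula in the Sample size calculation, one-sided alpha 0.025 and 80% power, n per group = 2 × [11.5 × (1.960 + 0.842) / distance]².
- Distance 4 + 1.1 = 5.1 gives 80 (81 with the t distribution), which is the stated 81. Then 81/0.8 = 101.25, rounded up to 102, as stated.
- With EA worse by 1.1, as the quoted falls imply, the distance is 4 - 1.1 = 2.9 and n is 247.

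That discrepancy is a separate matter and nothing below depends on it. I use 81 per arm because it is the stated evaluable number.

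**3. What the within-arm test can detect.** Inputs: 81 patients, SD 11.5, two-tailed 2.5% level (Statistical analysis).
- Standard error = 11.5/√81 = 1.28.
- Critical t on 80 df is about 2.28, so a mean fall of about 2.28 × 1.28 = 2.9 points is significant.
- The fall quoted for EA gives t = 10.2/1.28, or about 8.

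A significant result is close to assured if falls are near those quoted, and it says nothing about how much of the fall is due to EA.

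**4. What meeting the margin shows.** Let d be ESC's effect over placebo, which is not in the documents. Suppose EA has no specific effect, so it is truly worse than ESC by d. Then

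P(non-inferiority declared) = Φ((4 - d)/SE - 1.96), with SE = 11.5 × √(2/81) = 1.807.

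| Assumed d | (4 - d)/SE - 1.96 | Probability |
|---|---|---|
| 1 | 1.660 - 1.96 = -0.30 | 38% |
| 2 | 1.107 - 1.96 = -0.85 | 20% |
| 3 | 0.553 - 1.96 = -1.41 | 8% |
| 4 | 0 - 1.96 = -1.96 | 2.5% |
| 5 | -0.553 - 1.96 = -2.51 | 0.6% |

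Sensitivity, for d = 1, 2, 3, 4:
- 102 per arm, SD 11.5: 46%, 24%, 9%, 2.5%.
- 81 per arm, assumed SD 6 (not in the documents): 89%, 56%, 18%, 2.5%.

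The result turns on whether d is above or below 4. Below 4, an EA with no specific effect passes more often than 2.5%; above 4, less often. The document gives no figure from which to tell.

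**The case against.** The case for the plan is substantial. A two-arm active-controlled non-inferiority trial is a legitimate design. The Hypothesis section, the Abstract's introduction and the Discussion all frame the question as EA against escitalopram, and the arms are described fully enough that few readers would imagine a third. This stands. It limits the point to one wrong label and to over-wide wording in the Design and Conclusion sections.

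Four stronger readings are tempting, and the documents do not support them.

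- *Natural recovery and non-specific response bias the trial's main result.* They act in both arms and do not bias the randomised EA-ESC difference. They affect only statements about EA on its own.
- *The paired t-tests are planned as proof of efficacy.* The Statistical analysis section lists them without saying what they are to establish, and it also plans between-group comparisons.
- *The margin exceeds ESC's true effect, or rests on uncontrolled data.* No ESC-placebo effect is given, so the values of d are assumptions. At d = 4 the error is the nominal 2.5%, and beyond that it is smaller. The quoted falls come from one earlier study with a medication group and an EA group; its design is not visible here, nor is how 4 was reached.
- *A non-inferior EA could more than halve recovery.* With an assumed entry mean of 20.5 and an 11.3-point fall, the mean is 9.2; 4 points worse is 13.2. The share scoring 7 or below, Φ((7.5 - mean)/SD), goes from 39% to 17% at an assumed SD of 6, but from 44% to 31% at the document's SD of 11.5. Moreover, a true 4-point deficit passes only 2.5% of the time. At SD 11.5 the observed deficit must be under 4 - 1.96 × 1.807 = 0.46 points.

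**Conclusion.** The point holds in a limited form. Placebo-controlled is the wrong description of these arms. The trial can answer whether EA is non-inferior to ESC within the stated margin. It cannot by itself establish that EA is efficacious, as the Design section's separate aim and the Conclusion's expectation would have it. The only other evidence planned is within-arm change, which is uncontrolled, and the margin is not linked to a stated ESC-placebo effect.

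The size is illustrative: about 38%, 20%, 8% or 2.5% chance that an EA with no specific effect is declared non-inferior when ESC's specific effect is 1, 2, 3 or 4 points, and lower above 4. This assumes 81 per arm, SD 11.5, normal theory and a one-sided 0.025 test, which is the reading the sample-size formula implies. The conclusion about labels and aims rests on the text alone and needs none of these assumptions. It is a correction to what may be claimed and does not invalidate the randomised comparison.

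**What to change.** 1. In the Introduction, replace placebo-controlled with active-controlled, double-dummy.
2. In the Design and Conclusion sections, restrict the efficacy aim and the expected conclusion to whether EA is non-inferior to ESC within the stated margin on HAMD-17 change from baseline to week 12. Add to the limitations that, without a placebo reference or a margin tied to the ESC-placebo effect, non-inferiority alone does not show that EA is effective.
3. In the Statistical analysis section, make within-arm changes descriptive and state that they are not tests of efficacy.

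No new arm is needed for this narrower claim, and recovery rate need not become a second success criterion. Reporting the already planned week-12 recovery comparison as a difference with a confidence interval is enough.

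The cost is a change of wording, with no extra patients, visits or data. The downside is a narrower claim.

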## Methods and analysis

### Hypothesis

We aim to provide definitive proof to validate the hypothesis that EA is not inferior to escitalopram (ESC) in the treatment of mild to moderate first-episode depression.

### Design

This is a multi-center, patient-assessor-blinded, randomized, and controlled trial designed to evaluate the efficacy and safety of EA treatment in patients with mild to moderate first-episode depression and to compare the therapeutic effect between EA and ESC.

We will conduct this study at 4 centers, including Shanghai Municipal Hospital of Traditional Chinese Medicine, Shanghai Mental Health Center, Shanghai Pudong New District Nanhui Mental Health Center, and Shanghai Xuhui District Central Hospital. A total of 204 patients who meet the inclusion criteria will be recruited and randomly assigned into either group, receiving EA treatment with placebo drugs or ESC with sham acupuncture (SA) treatment. After a one-week baseline evaluation, participants will enter a nine-month observation period in this trial. Participants will receive the EA or SA treatment three times a week (every other day) for the first 8 weeks and twice a week (every two days) for the final 4 weeks. Participants will be assessed at the following time points: baseline (1 week before treatment), the 1st month of treatment (4 weeks after treatment starts), the 2nd month of treatment (8 weeks after treatment starts), the end of treatment (12 weeks after treatment starts), and follow-up (1 month, 3 months, and 6 months after treatment ends). All participants will complete the self-rated scales to assess their mental state and quality of life (see the detailed trial process in **Figures 1**, **2**). Throughout the trial, we will adhere to the Standards for Reporting Interventions in Clinical Trials of Acupuncture (STRICTA).

**Figure 1 f1:**
[figure not shown]
Schedule of enrolment, interventions, and assessments. EA, electroacupuncture; ESC, escitalopram; HAMD-17, 17-item Hamilton Rating Scale for Depression; PHQ-9, The Patient Health Questionnaire-9; SF-36, 36-Item Short Form Survey Instrument.

**Figure 2 f2:**
[figure not shown]
Flowchart of the study. EA, electroacupuncture; SA, sham acupuncture; ESC, escitalopram; HAMD-17, 17-item Hamilton Rating Scale for Depression; PHQ-9, The Patient Health Questionnaire-9; SF-36, 36-Item Short Form Survey Instrument; TESS, Treatment Emergent Symptom Scale.

### Patients

#### Inclusion criteria

Participants meeting the following criteria will be included:

Participants of either gender, aged between 18 and 60 years.Participants with psychiatrist-diagnosed depression based on the DSM-5 criteria (10).Participants whose HAMD-17 score is between 17–24.Participants who have not previously taken any type of antidepressant.Participants who are assessed as having a low risk of suicide (i.e., score ≤ 2 in the Hamilton question of suicide).Participants who have not received acupuncture treatment for at least 1 year.Participants who are willing to participate in the trial and sign a written informed consent.

#### Exclusion criteria

Participants who indicate the presence of any of the following conditions will be excluded:

Participants with secondary depressive disorder caused by organic or psychotic disorders and other diseases.Participants who are in the depressive episode of bipolar disorder or suffering from dysthymia, reactive depression, or depressive syndrome caused by other diseases.Participants who had severe liver, kidney, heart, brain, or other organic diseases.Participants with a history of alcohol abuse or drug dependence.Pregnant or lactating women.

### Recruitment

The recruitment of participants will be conducted via the official websites of the centers, as well as through advertisements from outpatient clinics located within hospitals. Patients with depression who express interest in participating in the study are required to have a phone or online interview first. And then they will be asked to participate in face-to-face screening, during which they will be required to fill out forms with the guidance of psychologists or trained physicians. Before starting the intervention, participants who meet the eligibility criteria will be required to provide written informed consent.

### Sample size calculation

The non-inferiority hypothesis is based on the results of a previous study (11). HAMD-17, as the primary outcome, decreased by 11.3 points in the premedication group and by 10.2 points in the EA group, with an equal standard deviation of 11.5 points. Following these parameters, the proposed non-inferiority boundary is set at -4 points, with a level one type I statistical error equivalent to 0.025 and a desired statistical power standing at 80%. These calculations are supported by the analytical tools implemented in PASS 15.0. The results were obtained for a required sample size of 81 cases per group, and considering a 20% drop rate, 102 cases need to be included in each group, totaling 204 cases. The formula employed to determine the sample size in this trial was listed as:

$${\text{n}}_{\text{A}}={\text{k}}_{{\text{n}}_{\text{B}}}\;\text{and}\;{\text{n}}_{\text{B}}=\left(1+\frac{1}{\text{k}}\right){\left(\sigma \frac{Z_{1-\alpha }+Z_{1-\beta }}{\mu_{A}-\mu_{B}-\delta }\right)}^{2}$$

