### Randomization and blinding

This study uses a single-blind design, concealing group allocations from participants. Only acupuncturists will be aware of the assignments, but they will not be involved in any other part of the trial, including enrollment, evaluation, and data analysis. To increase blind validity, treatment will be performed in a separate room. Meanwhile, communication about the treatment or efficacy between acupuncturists and participants will be avoided to the maximum extent. At the conclusion of the 12-week intervention, the Bang blinding index will confirm the effectiveness of the blinding technique (12). The placebo drugs supplied by Shanghai Xinyi Huanghe Pharmaceutical Co. Ltd. have an identical appearance to the proprietary form of ESC (Bailote), which is supplied by Sichuan Kelun Pharmaceutical Co. Ltd. All medications are regularly dispensed once a week, with seven tablets per box. Patients can pick up their medication from the dispenser at their own corresponding number on the pre-packaged envelopes. Before the start of the trial, each investigator will receive multiple training sessions on the implementation of the standards of this study and will strictly adhere to the principle of separation of departments.

The study will use a block randomization method with a block size of four, facilitated by SPSS version 24.0 software. Eligible participants will be randomly assigned to either the EA or ESC group in equal proportions. An independent researcher will enclose the treatment allocation codes in sequentially numbered opaque envelopes, and another independent researcher will assign participants to the groups based on the corresponding number on the pre-packaged envelopes and randomization schedule. To confirm the effectiveness of the blinding, the acupuncturist will inquire with all participants whether they received EA or SA treatment at the end of the trial. All participants’ information will remain confidential to the acupuncturist and assessors throughout the trial.

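### The 81 per arm assumes EA is 1.1 points better than the drug, but the stated inputs say 1.1 points worse; on those inputs power is about 36%, not 80%

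*Protocol article*

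**What the plan says.** All the planning inputs stand in the protocol article under Sample size calculation. Citing an earlier study, the section reports that "HAMD-17, as the primary outcome, decreased by 11.3 points in the premedication group and by 10.2 points in the EA group". The SD is put at 11.5 in both arms. For the margin, the text has "the proposed non-inferiority boundary is set at -4 points". The type I error is 0.025 and the target power 80%. The stated outcome reads "The results were obtained for a required sample size of 81 cases per group". Allowing for 20% dropout, this becomes 102 per arm, or 204 in total. The section prints a formula whose denominator is mu_A - mu_B - delta, without saying which arm is A. Under Randomization and blinding, "Eligible participants will be randomly assigned to either the EA or ESC group in equal proportions", so k = 1.

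The Hypothesis section and the Discussion both frame the question as EA being non-inferior to escitalopram. Under Primary outcome, a higher HAMD-17 score means worse depression, so a larger decrease is better.

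**The concern.** A decrease of 10.2 on EA against 11.3 on the comparator means that EA is expected to do slightly worse. In a non-inferiority trial, an expected deficit uses up part of the margin and raises the sample size above that for equal arms. Here the published number is below the one for equal arms, which can happen only if the new treatment is assumed to be better.

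At stake is the basis for the trial's main claim. If the cited means and SD are right, the trial is more likely than not to miss non-inferiority even when EA lies well inside the margin. A reader who believes the trial had 80% power could then take that result as evidence against EA.

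**Working it through.** **Inputs** (Sample size calculation, except where noted): mean decrease 11.3 (comparator) and 10.2 (EA); SD 11.5; margin 4 points; alpha 0.025, taken as one-sided because the formula uses Z(1-alpha); power 80%; k = 1 (Randomization and blinding); 81 evaluable and 102 randomised per arm.

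**Formula.** With k = 1, n per arm = 2 × [11.5 × (1.960 + 0.842) / d]², where d is the distance from the assumed true difference to the margin. The t-based figures use the noncentral t distribution.

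**Reproducing the plan's figure.** Taking the drug arm as A and delta = -4, d = 11.3 - 10.2 + 4 = 5.1. The formula gives 79.8, so 80 per arm; the t-based version gives exactly 81, with 80.1% power. The dropout step also reproduces: 81 / 0.8 = 101.25, so 102.

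**The direction in the text.** For EA non-inferior to the drug, the difference is EA minus drug in points of improvement: 10.2 - 11.3 = -1.1. Then d = -1.1 - (-4) = 2.9, and n = 246.9, so 247 per arm (t: 248).

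**Required n and power side by side** (SD 11.5, one-sided 0.025):

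| Assumed truth | d | n per arm for 80% power (z / t) | Power at 81 per arm (z / t) |
|---|---|---|---|
| EA 1.1 points worse (as the text says) | 2.9 | 247 / 248 | 36.1% / 35.8% |
| No difference | 4.0 | 130 / 131 | 60.0% / 59.5% |
| EA 1.1 points better | 5.1 | 80 / 81 | 80.6% / 80.1% |

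Power by the normal approximation is Φ(d / SE - 1.960), with SE = 11.5 × √(2/81) = 1.807. For d = 2.9 this is Φ(1.605 - 1.960) = Φ(-0.355) = 36.1%.

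**Other readings of alpha.** One-sided 0.05 gives 195, 103 and 63 per arm for the three rows (z). One-sided 0.0125 gives 299, 158 and 97. None is 81.

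**With dropout.** 247 / 0.8 = 308.75, so 309 per arm; 248 / 0.8 = 310. The total is 618 to 620, against the planned 204.

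**If all 102 per arm were analysed.** SE = 11.5 × √(2/102) = 1.610, and power at d = 2.9 is 43.7% (z) or 43.3% (t).

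**SD at which 81 per arm would suffice with d = 2.9.** 2.9 × √(81/2) / 2.802 = 6.59 (z), or about 6.55 (t).

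**Plausibility of SD 11.5.** The inclusion criteria limit baseline HAMD-17 to 17-24, and the scale starts at 0, so no patient can improve by more than 24 points. Yet 10.2 + 2 × 11.5 = 33.2. If 11.5 is meant as the SD of change, it fits this population poorly.

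**The case against.** The arithmetic is not in dispute, and nothing else in the article corrects it. Five points can be made against the conclusion.

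- **Cause.** The article shows that text and calculation run in opposite directions, not which of them slipped. The arm labels could be swapped in the sentence, or 11.3 and 10.2 could be end scores misdescribed as decreases; either would put EA 1.1 points ahead and make 81 right. The undefined label for the comparator group makes a wording fault credible. This stands: only the source study can settle it. It does not remove the contradiction, and a design that reaches 80% only by assuming EA is better would need to say so.
- **Formula.** It never defines A, so 5.1 is a literal reading with the first-named group as A. True, but for the stated hypothesis that reading measures the drug against EA, the wrong way round.
- **Analysed number.** The Statistical analysis section carries the last observation forward for anyone treated once with one outcome assessment, so more than 81 per arm may be analysed. The ceiling is about 43% to 44%, still far below 80%. The plan's own evaluable number is 81.
- **Alpha.** The same section sets 2.5% with two-tailed testing for all analyses. Read as one-sided 0.0125, power at 81 per arm falls to about 26%. The 36% therefore uses the more favourable reading.
- **SD.** If 11.5 is too large, true power may be adequate. Possibly, but the article gives no smaller value, and two errors that may offset each other do not support a claim of 80%.

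**Conclusion.** The concern holds. The stated means, margin and sample size cannot all be right: 81 per arm follows from a 1.1-point advantage for EA, while the text gives a 1.1-point disadvantage. On the stated inputs, 81 evaluable per arm gives about 36% power, and 80% needs 247 to 248 per arm, about three times as many.

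This assumes that the comparator in the quoted sentence is the drug arm standing in for escitalopram, that both figures are improvements as the wording says, and that 0.025 is one-sided. The SD remark is a separate weakness; the contradiction does not depend on it.

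**What to change.** 1. Check the two means against the source study. If the sentence is right, correct the calculation to a distance of 2.9 points. If the sentence is reversed, correct it and state openly that the 80% rests on EA being 1.1 points better.
2. Define arms A and B and the sign of delta in the formula.
3. Restate the power of 204 patients. On the present inputs it is about 36% with 81 evaluable per arm (about 43% if all 102 are analysed), and about 59% at no difference with 81 per arm.
4. Reconcile the one-sided 0.025 used here with the two-tailed 2.5% in the Statistical analysis section.
5. Replace 11.5 with a justified SD of change that fits the 17-24 entry band and, if covariance analysis is the primary method, allows for baseline adjustment. Where data are accruing, check it on blinded pooled data. If it is about 6.5 or less, 81 per arm stands on the stated means; if not, report the lower power.

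The cost is a text correction, a blinded SD check and a less favourable power figure. Making the statement correct needs no increase in enrolment.
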